## Abstract

**Introduction:**

We describe a protocol for FIRE CORAL, an observational cohort study that examines the recovery from COVID-19 disease following acute hospitalization with an emphasis on functional, imaging, and respiratory evaluation.

**Methods and analysis:**

FIRE CORAL is a multicenter prospective cohort study of participants recovering from COVID-19 disease with in-person follow-up for functional and pulmonary phenotyping conducted by the National Heart, Lung and Blood Institute (NHLBI) Prevention and Early Treatment of Acute Lung Injury (PETAL) Network. FIRE CORAL will include a subset of participants enrolled in Biology and Longitudinal Epidemiology of PETAL COVID-19 Observational Study (BLUE CORAL), an NHLBI-funded prospective cohort study describing the clinical characteristics, treatments, biology, and outcomes of hospitalized patients with COVID-19 across the PETAL Network. FIRE CORAL consists of a battery of in-person assessments objectively measuring pulmonary function, abnormalities on lung imaging, physical functional status, and biospecimen analyses. Participants will attend and perform initial in-person testing at 3 to 9 months after hospitalization. The primary objective of the study is to determine the feasibility of longitudinal assessments investigating multiple domains of recovery from COVID-19. Secondarily, we will perform descriptive statistics, including the prevalence and characterization of abnormalities on pulmonary function, chest imaging, and functional status. We will also identify potential clinical and biologic factors that predict recovery or the occurrence of persistent impairment of pulmonary function, chest imaging, and functional status.

**Ethics and dissemination:**

FIRE CORAL is approved via the Vanderbilt University central institutional review board (IRB) and via reliance agreement with the site IRBs. Results will be disseminated via the writing group for the protocol committee and reviewed by the PETAL Network publications committee prior to publication. Data obtained via the study will subsequently be made publicly available via NHLBI’s biorepository.

**Strengths and limitations of the study:**

**Strengths:**
First US-based multicenter cohort of pulmonary and functional outcomes in patients previously hospitalized for COVID-19 infectionLongitudinal biospecimen measurement allowing for biologic phenotyping of abnormalitiesGeographically diverse cohort allowing for a more generalizable understanding of post-COVID pulmonary sequela

**Limitations:**
Selected cohort given proximity to a participating centerSmall cohort which may be underpowered to identify small changes in pulmonary function

## Introduction

The long-term consequences of the novel coronavirus SARS-CoV-2 (COVID19) pandemic are yet to be fully realized. Heterogeneous manifestations of disease and syndromes following SARS-CoV-2 infection are common, increasingly recognized, and may be defined in the broadest sense as a failure to return to baseline level of health [1]. Driven in part by unprecedented patient-led advocacy and unprecedented numbers of patients [1–4], there has been increased attention to understanding and treating long-term sequelae of COVID-19, referred to variously as post-acute sequelae of COVID-19 (PASC), post-acute COVID, Long COVID, or long-haul COVID [5]. For example, the National Institutes of Health launched an initiative to advance understanding of PASC in December 2020. The current limited understanding of the diverse long-term sequelae of COVID-19 is a fundamental barrier to improve recovery for patients with PASC.

While the number of investigations focused on patient-reported outcomes is growing, relatively few have reported the results of objective assessments after hospital discharge for patients surviving severe COVID-19 disease [3, 4, 6–8]. Further, most cohorts to date enroll patients with ongoing symptoms rather than the full spectrum of recovery including asymptomatic patients. Despite the high prevalence of COVID-19 infection in the USA, there are limited reports of pulmonary function test (PFT) or computerized tomography (CT) imaging results following hospitalization for COVID-19 with few analyses investigating the relationship between lung function or chest imaging abnormalities and persistent respiratory symptoms. Few US-based cohorts [9] describe integrative functional assessments, such as 6-min walk tests, or longitudinal changes in biomarkers of recovery after hospital discharge.

To address this urgent need for studies that advance understanding of the clinical spectrum of PASC, we describe a protocol for a prospective observational study, the Functional, Imaging, and Respiratory Evaluation (FIRE) of hospitalized patients following COVID-19 (FIRE CORAL), to (1) examine the feasibility of longitudinal assessments investigating multiple domains of recovery in parallel and (2) elucidate the recovery from COVID-19 disease following acute hospitalization with an emphasis on functional, imaging, and respiratory evaluation. The study procedures and assessments chosen by our investigative team for this protocol measure impairments and syndromes commonly described by patients during routine clinical care following COVID-19.

## Methods and analysis

### Study design

FIRE CORAL is a multicenter prospective cohort study of participants recovering from COVID-19 disease with in-person follow-up for functional and pulmonary phenotyping (Table 1). The cohort is comprised of participants who were enrolled and completed study requirements for the National Heart, Lung and Blood Institute (NHLBI) funded BLUE CORAL study (see details below).

**Table 1 Tab1:**
[figure not shown]
Study procedures for BLUE CORAL, BLUE LTO, and FIRE CORAL

Definitions:

• BLUE CORAL—1390 patient prospective study beginning during acute SARS-CoV2 infection hospitalization

• BLUE LTO—800 patient subset of BLUE CORAL participating in post-hospital telephone follow-up via long-term outcomes team

• FIRE CORAL—80 patient subset of BLUE CORAL LTO, returning for in person assessments

^a^The visit occurring 6–9 months after hospital discharge is optional and only performed if patient completes first FIRE CORAL visit between 3 and 6 months after hospital discharge

bThe visit occurring 12 months after hospital discharge is performed after the previous and at least > 2 months later (window from 11 to 15 months)

Sites from the NHLBI Prevention and Early Treatment of Acute Lung Injury (*PETAL)* Network that are participating in the BLUE CORAL study and have the capabilities of performing study procedures are eligible to participate in the FIRE CORAL study on a volunteer basis. Briefly, PETAL is a research network of 12 Clinical Centers and 1 Clinical Coordinating Center funded by the NHLBI that was initially developed to test prevention and early treatment strategies for patients with or at risk for acute respiratory distress syndrome (ARDS) and during the pandemic expanded to include COVID19 studies including this observational study. Additional information on PETAL network including purpose, coordination, leadership, study oversight, and general study procedures been previously described online (https://petalnet.org/ and https://petalnet.org/studies/public/firecoral).

### Blue coral

BLUE CORAL was a prospective cohort study of up to 1390 hospitalized participants with COVID-19 disease; follow-up of participants is ongoing. The primary aim of BLUE CORAL was to describe the clinical characteristics, treatments, biology, and outcomes of participants hospitalized with COVID-19 infection. Secondarily, BLUE CORAL aimed to identify clinical and biologic risk factors for adverse COVID-19 outcomes and persistent symptoms. These predictors will be used to understand trajectories of recovery and a de-identified repository of biospecimens and clinical data will be established for rapid sharing. Adults (age ≥ 18 years) requiring hospitalization with symptomatic COVID-19 disease were eligible for BLUE CORAL enrollment within 72 h of study hospital admission. Prisoners and patients on hospice/comfort-focused care were excluded. Data on demographics, baseline function, clinical parameters, management, and clinical outcomes as well as biologic specimens were collected during the hospitalization. In addition, participants and/or proxies participate in telephone post-hospital follow-up assessments coordinated between two central call centers at University of Michigan and Oregon Health and Science University at 1, 3, 6, and 12 months after hospital discharge (Table 1). These telephone surveys include assessment of quality of life, ability to participate in activity of daily living including new impairments or disabilities, ongoing symptomology, e.g., dyspnea and fatigue, emotional health symptoms, cognitive function, financial strain/return to employment, and need for rehospitalization.

### FIRE CORAL study aim

The objectives of the FIRE CORAL study are:Primary: To examine the feasibility of conducting rigorous in-person follow-up testing of participants discharged from the hospital following COVID-19 illness to assist with planning for a larger study to evaluate variables associated with differential recoverySecondary: To describe the pulmonary, imaging, and functional recovery following COVID-19 hospitalization in a diverse population of patients. FIRE CORAL extends the BLUE CORAL study follow-up to include in-person study visits for pulmonary phenotyping and functional assessment

### Study setting

Ten PETAL Network hospitals geographically spread out across the US are set to participate in FIRE CORAL (Fig. 1). FIRE CORAL will enroll 80 participants from among the cohort of BLUE CORAL participants who survive their hospitalization and are participating in the BLUE CORAL long-term outcomes cohort.

**Fig. 1 Fig1:**
[figure not shown]
Geographic distribution of participating FIRE-CORAL sites

### Inclusion criteria

We will enroll adult participants with a recent COVID-19 hospitalization who were enrolled in the BLUE CORAL study and completed the 1- or 3-month post-hospital telephone long-term outcomes assessment (Fig. 2A). Participants are eligible for FIRE CORAL if they speak English or Spanish as their primary language and are cleared to attend in-person testing per each local site’s specific COVID-19 infection control criteria. Participants with pre-existing severe disability defined by reduced ADLs and/or cognitive impairment were excluded from post-hospital follow-up and thus not included in FIRE CORAL.

**Fig. 2 Fig2:**
[figure not shown]
Study inclusion and screening timeline and process. **a** Timeline of eligibility for enrollment in BLUE and FIRE CORAL. **B** Process for site screening and participation based on COVID infection status

### Exclusion criteria

We will exclude participants unable or unwilling to return to the clinical site for testing, participants unable to follow instructions as reported by caregiver, surrogate or investigator, and participants that self-report pregnancy at time of screening or follow-up visit given the radiation risks associated with CT scans in this population.

### Screening, recruitment, and informed consent

The BLUE CORAL long-term outcome coordinating center will notify FIRE CORAL sites of participants completing the 1- or 3-month telephone assessment for BLUE CORAL who are potentially eligible for participation in FIRE CORAL. Use of a centralized screening center with an empaneled cohort that is already engaged in telephonic follow-up is a unique feature of the FIRE-CORAL cohort (Fig. 2B). This approach aims to improve the likelihood of cohort retention in longer-term post-hospital/ICU follow-up. Once an eligible participant is identified, the participating FIRE-CORAL sites will connect with the eligible participant using a phone script to introduce the study and determine eligibility for inclusion. Those who express interest in participation will be scheduled for an in person visit for study procedures. Informed consent will be obtained from the participant or from a surrogate decision maker if the participant lacks decision-making capacity at the time of the in-person visit.

### Study procedures

*FIRE CORAL* consists of a battery of in-person assessments objectively measuring pulmonary function, abnormalities on lung imaging, and functional status. Participants will attend and perform initial in-person testing at 3 to 9 months after hospital discharge (Table 1, Fig. 3). Participants with abnormal findings on pulmonary function testing or chest imaging during their initial assessment or those with persistent respiratory symptoms will be eligible to repeat study procedures 3 months later with a subsequent visit at 12 months. All participants will be invited to return for in-person follow-up at 12 months after hospital discharge. Imaging and clinical assessments performed as part of routine clinical care within the specified study timeframe will be used in lieu of dedicated study procedures.

**Fig. 3 Fig3:**
[figure not shown]
Study day procedures. SGROQ, Saint George’s Respiratory Questionnaire; SPPB, short physical performance battery; PFT, pulmonary function tests; 6WMT, 6-min walk test; CT, commuted tomography

Tests and measures are summarized below:

*A high-resolution chest CT scan* will be performed without contrast to assess residual abnormalities of the lungs according to local clinical protocol. Specifications for site-specific CT protocols were provided by a central radiologist to promote standardization across sites (Table 2) [10]. CT scans will be interpreted by the site radiologist and then subsequently sent via a central repository for standardized reading and scoring by expert chest radiologists at National Jewish Hospital in Denver, CO. These investigators will employ a standard scoring approach developed at National Jewish Hospital for COVID-19 abnormalities as summarized in Table 2. All lung zones will be scored for abnormalities with the extent of involvement quantified to the nearest 10%.

**Table 2 Tab2:** High-Resolution Chest CT Scoring Criteria developed by National Jewish Hospital, Denver, CO

	RUZ	LUZ	RMZ	LMZ	RLZ	LLZ
Normal attenuation						
**Non-fibrotic abnormality**						
Ground-glass attenuation						
Consolidation						
Ground-glass attenuation with reticular abnormality						
Reticular abnormality						
**Fibrotic abnormality**						
Ground glass abnormality with traction bronchiolectasis/bronchiectasis and/or architectural distortion						
Consolidation with traction bronchiolectasis/bronchiectasis and/or architectural distortion						
Reticular abnormality with traction bronchiolectasis/bronchiectasis and/or architectural distortion						
Honeycombing						
**Other**						
Emphysema						
Cysts/pneumatoceles						
Mosaic attenuation						
Expiratory air trapping						
Pleural effusion: right versus left						
Pneumothorax: right versus left						
Pleural thickening: right versus left						
Mediastinal adenopathy						

Extent of each abnormality is scored in each zone to the nearest 10%, *RUZ* Right upper zone, *LUZ* Left upper zone, *RMZ* Right middle zone, *LMZ* Left middle zone, *RLZ* Right lower zone, *LLZ* Left lower zone

*PFTs* will be performed and will include spirometry, lung volume assessment, and diffusing capacity measured by single breath measurement. These will be collected by the site study teams and reviewed centrally by the research team.

*Six Minute Walk Test (6MWT)* is a valid and reliable measure of functional and exercise capacity in survivors of acute respiratory failure [11]. Participants will undergo the 6MWT per guidelines of the American Thoracic Society [12]. The estimated minimal important difference (MID) for survivors of critical illness ranges between 20 and 30 m, which equates to 3 to 5% of the percent achieved of their calculated predicted distance [11].

*Short Physical Performance Battery (SPPB)* is a valid measure assessing lower-extremity physical function with scores ranging from 0 to 12. The SPPB includes three sub-components: 4-m habitual gait speed, standing balance, and chair-rise test [13, 14].

*St. George’s Respiratory Questionnaire (SGRQ)* is a self-report questionnaire assessing disease-specific health-related quality of life (HRQL) for patients with chronic lung diseases including chronic obstructive pulmonary disease, asthma, and bronchiectasis [15]. The SGRQ scores range from 0 to 100 with a lower score reflecting a better pulmonary-specific HRQL [16–18]. The MID has been proposed between 4 and 8.3 units for patients with COPD [19, 20]. THE SGRQ has been used to describe pulmonary disease-specific HRQL in survivors of ARDS [21].

*Functional Assessment of Chronic Illness Therapy-Fatigue (FACIT-F scale)* is a self-report measure assessing fatigue and the impact upon activities of daily living and function originally developed to examine cancer-related fatigue [22]. The FACIT-F scale has been validated and reliably utilized in patients with COPD [23, 24] and survivors of critical illness [25].

#### Biospecimen collection

Up to 15 mL of blood will be collected, which will include 6 mL of plasma, 2.5 mL for DNA PaxGENE, and 2.5 mL for RNA PaxGENE at each follow-up visit. The overarching goal for these biospecimens is to conduct analyses that advance understanding of the biological responses in participants recovering from severe COVID-19 and that correlate blood measures/biomarkers with clinical phenotypes of poor outcomes. Planned investigations include assessment of longitudinal inflammatory, immunologic or viral response; and evaluation of the association between biologic recovery and long-term symptoms.

#### Demographic and clinical data

Data collected during index hospitalization for the parent BLUE CORAL study will be utilized for participants enrolled in FIRE CORAL. We will abstract data on demographics, COVID testing and symptoms, comorbidities, home and hospital medications, vital signs including ventilator settings, lab values, intensive care interventions, and COVID-19 targeted treatments. All available pre-illness chest imaging, PFTs, and 6MWTs performed within the site’s healthcare system in the 10 years prior to hospital admission for COVID-19 will be collected to establish a pre-COVID-19 baseline for comparison.

#### Study optimization/training

An interdisciplinary protocol development committee was formed in January 2021 with oversight from the PETAL Network and NHLBI. The committee met weekly over the next three months to design the study, including selection and timing of in-person assessments. After the final protocol was approved by protocol committee consensus, the study protocol was reviewed and approved by the PETAL Network Steering Committee, the PETAL Network Data Safety and Monitoring Board, and NHLBI leadership before initiation of primary investigator and research personnel training. All sites across the PETAL Network were invited to participate on a voluntary basis. Personnel involved in the study were required to review the study manuals which included the standard operating procedures. In addition, all personnel attended a video-conference meeting that provided training on each phase of the study including training videos for selected outcome measures. The site initiation webinar and all training videos are readily available on the PETAL Network website.

### Statistical methods

#### Sample size

For this pilot study, the target enrollment was chosen to balance characterizing the range of PASC abnormalities against the time constraints associated with COVID-19 research and the waning pandemic with widespread vaccination. Based on these criteria, the target enrollment of 80 participants was felt to be sufficient to provide an urgently needed, preliminary understanding of longer-term respiratory manifestations after COVID-19 infection sufficient to guide future post-COVID pulmonary studies. Our sample size was purposefully chosen to be small to demonstrate the feasibility of conducting longitudinal in-person research in COVID survivors with an understanding that larger studies would be needed to define disease trajectories and identify clinical predictors with small effects [26]. The sample size of 80 was determined for based on multiple factors including the availability of participants enrolled in BLUE CORAL, the number of participating sites, and previous feasibility studies. Sample sizes for pilot and feasibility studies “should be representative of the target study population,” [27] and in general, there are limited evidence to justify sample size of feasibility studies [26]. Research on feasibility studies recommend sample size estimates based on a confidence interval approach: an expected completion rate of 75% with lower bound of the CI = 70%, a total of 75 participants would be needed [27]. Finally, Sim and Lewis suggest that a sample size of 50 should be utilized for pilot studies of randomized controlled trials (RCT) [28]. Our proposed feasibility study will be deemed successful if at least 50 participants out of proposed 80 (62.5%, 95% CI 52–73%) complete at least one study visit.

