#### Statistical analysis plan

To examine the feasibility of long-term follow-up, we will describe the number of participants enrolled and the proportion that returned for in-person follow-up (primary objective). We will perform summary or descriptive statistics to describe the prevalence of abnormalities of pulmonary function, chest CT imaging, and functional status in the enrolled participants (secondary objective). Among participants who return for a 12-month visit, we will describe the trajectory of recovery of pulmonary function and functional status between first and last study visits. Additionally, we will test the relationships (correlative analyses) between outcomes with key independent variables including participant demographics, severity and duration of illness, pre-hospital function, and exposure to in-hospital and post-hospital interventions. Correlative testing and regression analyses will be performed only as *exploratory* to examine relationships between potential predictors and participant outcomes. In addition, repeated measures analyses will be explored to examine change over time. Our small sample size will limit our ability to perform multivariable testing with all potential confounding variables but will allow for identification of potentially important predictors and sample size justification for future larger studies. Our proposed sample is large enough to demonstrate feasibility of longitudinal follow-up, estimate the prevalence of abnormalities after COVID-19 for the purposes of planning, and identify longitudinal trends in recovery and potentially important predictors for future analyses. All analytic plans will be agreed upon by the FIRE CORAL committee after review of the distribution of abnormalities from the first 40 completed visit.

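### The confidence-interval figure offered in support of n=80 (75% completion, lower bound 70%, 75 participants) matches no conventional confidence level; at 95% the lower limit is about 65%

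*Protocol article*

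**What the plan says.** The Sample size section of the protocol article gives several reasons for enrolling 80 participants.

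- **Practical grounds.** It attributes the number to "multiple factors including the availability of participants enrolled in BLUE CORAL, the number of participating sites, and previous feasibility studies".
- **A precision argument.** It says that "Research on feasibility studies recommend sample size estimates based on a confidence interval approach", and continues with "an expected completion rate of 75% with lower bound of the CI = 70%, a total of 75 participants would be needed". A reference is cited. No confidence level is given.
- **A second citation**, which suggests 50 participants for pilot studies of randomised trials.
- **A success rule.** Feasibility is declared if at least 50 of 80 participants complete at least one visit. The proportion and interval shown with it are "62.5%, 95% CI 52–73%", so here the 95% level is named.

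**The concern.** An expected rate, a lower confidence limit and a sample size are tied together by one formula once a confidence level is chosen. For a proportion near 75%, a distance of 5 points from estimate to limit is tight for 75 people. The 95% interval printed for 50 of 80 runs from 52% to 73%, about 10 points on either side. A slightly smaller sample cannot be about twice as precise at 75%, where the variance is only modestly lower (0.1875 against 0.2344).

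Feasibility is the primary objective, and the study is meant to help plan a larger one. A reader who takes the sentence at face value would expect 75 to 80 participants to rule out completion below 70% if 75% is observed. A planner who reused it at the 95% level would recruit about a quarter of the number needed (75/289 = 0.26).

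**Working it through.** **Inputs, all from the Sample size section**

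- Expected completion p = 0.75
- Lower limit 0.70, so distance d = 0.75 − 0.70 = 0.05
- Number said to be needed n = 75; planned enrolment 80
- Confidence level for this figure: not stated. I take two-sided 95% as the main case because it is the only level named in the paragraph, and show others.

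**1. Reproducing the plan's figure**

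The usual formula is n = z² p(1 − p)/d².

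- With z = 1: 0.1875/0.0025 = 75 exactly.
- Equivalently, SE = √(0.75 × 0.25/75) = 0.0500, and (0.75 − 0.70)/0.0500 = 1.00.

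So 70% is the estimate minus one standard error. That corresponds to 68.3% two-sided or 84.1% one-sided confidence. The figure is what one obtains if the z multiplier is left out.

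**2. Number needed for a 70% lower limit at usual levels (Wald)**

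| Level | z | n |
|---|---|---|
| One-sided 80% | 0.842 | 54 |
| Two-sided 80% / one-sided 90% | 1.282 | 124 |
| Two-sided 90% / one-sided 95% | 1.645 | 203 |
| Two-sided 95% | 1.960 | 289 |

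For two-sided 95%: 1.96² × 0.1875/0.0025 = 288.1, rounded up to 289. Wilson gives 323 and the exact (Clopper-Pearson) method 335. None of these is 75.

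**3. Lower limit that 75 participants do give**

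- Wald 95%: 0.75 − 1.96 × 0.0500 = 0.652 (half-width 9.8 points).
- 56 of 75 completing (74.7%): Wilson 63.8%, exact 63.3%.
- Two-sided 90%: 66.8%. Two-sided 80%: 68.6%.

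The pair of 75% and about 75 participants fits a 95% lower limit near 65%: with d = 0.10, 1.96² × 0.1875/0.01 = 72.03, so n = 73.

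**4. Precision at the planned 80**

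SE = √(0.1875/80) = 0.0484, and 1.96 × 0.0484 = 0.095. For 60 of 80:

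- Wald 65.5% to 84.5%
- Wilson 64.5% to 83.2%
- Exact 64.1% to 84.0%

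**5. Cross-check on the other interval in the paragraph**

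50/80 = 0.625; SE = √(0.625 × 0.375/80) = 0.0541; 0.625 ± 1.96 × 0.0541 = 51.9% to 73.1%. This reproduces the printed 52–73%, so the ordinary 95% Wald formula is evidently the one in use there.

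**6. Could a finite-population correction explain 75?**

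With n₀ = 288.1, n = n₀/(1 + (n₀ − 1)/N). For N = 800 (the telephone follow-up cohort) this is 212; for N = 1390 (all of BLUE CORAL) it is 239. It comes to 75 only for N of about 100 (N = 100 gives 74.4), a population the article does not mention.

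**The case against.** Several points on the other side stand.

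- **The 95% level is an inference.** The article gives only "lower bound of the CI = 70%" with no level. A reader might infer that the protocol claims 95% confidence for it and therefore that the precision is half of what was promised. The document does not say so. What can be said is that 80%, 90% and 95% two-sided, and 80%, 90% and 95% one-sided, all fail to give 75, and that an unlabelled confidence interval is not normally read as a 68% one.
- **The figure carries a citation.** The source is not at hand, so the slip may lie there, in transcription (70% written for 65%, say) or in an omitted level. This limits what can be said about its origin. The article still uses the number as support.
- **80 does not rest on this figure alone.** A reader might infer that the justification for 80 collapses. It does not: availability, number of sites and earlier studies are separate stated grounds. Nor is this the only precision statement, since the interval for 50 of 80 is labelled 95%, is computed at the actual sample size and is correct.
- **The success rule does not use the 70% bound.** It is a fixed count. If true completion is 75%, the binomial probability of at least 50 of 80 is 0.995; at 70% it is 0.94. Neither involves the 75-participant figure.
- **The Statistical analysis plan section does not repeat the error.** A reader might take its statement "Our proposed sample is large enough to demonstrate feasibility of longitudinal follow-up" as false on this account. That sentence cites no 70% bound and no 75 participants, and nothing here contradicts it.

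These points limit the consequence. None of them makes the printed numbers agree.

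**Conclusion.** The statement that "a total of 75 participants would be needed" for 75% completion with a 70% lower limit is wrong at every conventional confidence level tried, and holds only at one standard error. Under the assumed two-sided 95% level, the lower limit at 75 participants is about 65% rather than 70%, and the number required for 70% is about 3.9 times the one given (289/75); at two-sided 90% it is about 2.7 times (203/75). The direction of the result does not depend on the interval method, and Wilson and exact methods widen the gap.

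The weight is moderate. A supporting argument for the sample size is incorrect and could mislead whoever plans the larger study, but enrolment, the success rule and the descriptive analysis stay as they are.

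**What to change.** Keep enrolment at 80. Remove the sentence claiming a 70% lower bound from 75 participants, or correct it after checking the cited source, and name the confidence level. Suggested replacement: *With 80 participants and an expected completion rate of 75%, the two-sided 95% confidence interval is about 65.5% to 84.5% (Wald; Wilson 64.5% to 83.2%).* If the figure of 75 participants is kept, its 95% lower limit should be given as about 65%.

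The cost is one sentence of text and no additional participants. The stated precision becomes less favourable, and agrees with the roughly ten-point half-width already shown for the success rule.

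### The 50/80 success cut-off is not aligned with the 75%/70% completion benchmark cited beside it, and neither 75 nor 80 participants delivers that benchmark

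*Protocol article*

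**What the plan says.** All the figures stand in one paragraph of the protocol article, under Statistical methods, Sample size.

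- **Basis of the target.** "The sample size of 80 was determined for based on multiple factors including the availability of participants enrolled in BLUE CORAL", together with the number of sites and earlier feasibility work.
- **Benchmark.** It is introduced as advice from the literature: "Research on feasibility studies recommend sample size estimates based on a confidence interval approach". The figures given are "an expected completion rate of 75% with lower bound of the CI = 70%, a total of 75 participants would be needed". No confidence level is stated for that limit.
- **Rule of thumb.** The next sentence cites authors who "suggest that a sample size of 50 should be utilized for pilot studies of randomized controlled trials".
- **Success rule.** The study will be "deemed successful if at least 50 participants out of proposed 80 (62.5%, 95% CI 52–73"%), where a participant counts after completing one visit or more.

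The section gives no reason for choosing 62.5% and does not relate it to the 75% and 70%. The Statistical analysis plan section treats the primary objective descriptively, as the number enrolled and the proportion returning in person.

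**The concern.** The primary objective is feasibility, to help plan a larger study, and this is the only success criterion stated for it. The 75% and 70% are the only expected completion figures in the document, so a reader will judge a successful verdict against them. The rule works to a different standard: a result that just passes is statistically incompatible with 75% and lies below 70% as a point estimate.

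The number 50 also appears one sentence earlier, as a sample size for pilot randomized trials. Such a figure says how many to enrol, not what completion rate is acceptable. The text does not say that the cut-off came from there, but it offers no other source.

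At stake is what the feasibility verdict means, and whether the target of 80 has the precision that the cited benchmark suggests.

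**Working it through.** **Inputs**, all from the Sample size section: cut-off 50 of 80; printed interval 52–73% at 95%; benchmark 75% expected, lower limit 70%, 75 participants. Assumption: the benchmark's limit is taken as two-sided 95%, to match the printed interval. Other levels are shown in step 5.

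**1. Reproduce the printed interval.** Wald: p ± 1.96 × √(p(1 − p)/n), with p = 50/80 = 0.625.
- Standard error = √(0.625 × 0.375/80) = 0.0541.
- Interval = 0.625 ± 0.106 = 51.9% to 73.1%, which agrees with 52–73%.
- Other methods: Wilson 51.5–72.3%, Clopper-Pearson 51.0–73.1%, Jeffreys 51.6–72.5%.

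**2. Compare the cut-off with the benchmark.**
- The upper limit is 72.3–73.1% under every method, so 75% is excluded. Exact binomial: P(X ≤ 50 | n = 80, p = 0.75) = 0.009.
- The point estimate of 62.5% is below 70%, but 70% lies inside the interval: P(X ≤ 50 | n = 80, p = 0.70) = 0.092.
- The interval first reaches 75% at 52/80 (Wald, Clopper-Pearson) or 53/80 (Wilson). So only 50–51 of 80 (50–52 by Wilson) both pass and exclude 75%.

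**3. How often the rule passes.** Exact binomial P(X ≥ 50 | n = 80, p):

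| True completion | P(success) |
|---|---|
| 55% | 10.8% |
| 60% | 36.9% |
| 65% | 72.4% |
| 70% | 94.1% |
| 75% | 99.5% |

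**4. Precision at 75% observed completion.**
- n = 80 (60/80): 0.75 ± 1.96 × √(0.1875/80) = 0.75 ± 0.095 = 65.5% to 84.5%. To three decimals the limits are 0.655 and 0.845 (0.6551 and 0.8449 unrounded), so about 66–84%. The Wilson lower limit is 64.5% and the Clopper-Pearson 64.1%.
- n = 75: 0.75 − 1.96 × √(0.1875/75) = 0.75 − 0.098 = 65.2%.

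**5. Size needed for a 70% lower limit at 75%.** n = z² × 0.75 × 0.25/0.05².
- Two-sided 95%: 1.96² × 0.1875/0.0025 = 288.1, so 289.
- Two-sided 90% (one-sided 95%): 203.
- Two-sided 80% (one-sided 90%): 124.
- At n = 75 the standard error is √(0.1875/75) = 0.05, so a 5-point margin is exactly one standard error, or about a 68% two-sided interval.

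**6. What a 70% lower limit would demand as a success rule at n = 80.** It needs 64/80 (Wald) or 65/80 (Wilson, Clopper-Pearson). A true rate of 75% would reach these only 18% and 12% of the time.

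**The case against.** The strongest defence is that an expected rate and a minimum cut-off are different quantities, and a cut-off normally sits below what is expected. The rule also discriminates: it passes 99.5% of the time at a true 75% and 37% at 60%. This stands, and it rules out several stronger readings that a reader might infer.

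- **That the rule contradicts the study's own assumption.** The 75% and 70% are reported as a literature recommendation, and the target of 80 is attributed to several factors. The article never says that this study expects 75%.
- **That 70% is a floor the rule breaches.** It is a lower confidence limit around an expected 75%, which is a precision target and not a minimum acceptable rate. At 50/80 the interval still contains 70%.
- **That any successful result rules out 75%.** Only the lowest two or three passing counts do so.
- **That a later study would be under-sized by 20%** (0.75/0.625 = 1.20). Nothing says a later study would assume 75% after observing 62.5%. The proportion returning will be reported, and a planner can use it. The criterion is also one completed visit, not long-term retention.
- **That 50 was taken from the pilot-trial rule.** The sentences are adjacent, but the text does not make the link.

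The defence does not explain why 62.5% was chosen. Nor does it rescue the benchmark, whose 75 participants do not follow from its own inputs at two-sided 95% or 90%. A condensed article may leave detail to the full protocol, but these figures are printed and can be checked as they stand.

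**Conclusion.** The point holds as a misalignment. The cut-off of 62.5% is unexplained and not tied to the completion benchmark printed beside it. A result at the cut-off excludes 75% at the 95% level and lies below 70% as a point estimate. A true rate of 65% would be declared a success about 7 times in 10.

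The benchmark also lends the target of 80 a precision it does not have: the 95% lower limit at 75% completion is about 66%, not 70%, and reaching 70% would take about 289 participants, roughly 3.6 times the target (289/80).

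The pass probabilities are exact binomial and assume 80 enrolled participants who complete independently with a common probability. The precision figures assume a two-sided 95% level, which the article does not state for the benchmark. At two-sided 90% the requirement is still 203.

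**What to change.** If 50/80 is kept as the single criterion:

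- Remove the 75%/70%/75-participant justification, or restate it with the precision actually achieved: at 75% observed completion, 80 participants give a 95% CI of about 66–84%.
- State that just meeting the criterion shows only that first-visit completion exceeds about 52%.
- Give the reason for choosing 62.5%.

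Graded progression zones are an option, but the investigators would have to justify the boundaries. For example, a top zone starting at 60/80 would be missed 44% of the time at a true rate of 75% (1 − 0.56).

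The change is wording only, with no effect on enrolment or procedures. The cost is that the stated precision, and what a successful verdict means, become less favourable.
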